### Safety

Every neonate admitted to the NICU will complete the TORCH screen for toxoplasma, rubella, cytomegalovirus, and herpes simplex, and mothers will be asked about CMV during screening. During the fresh milk feeding, human milk will be monitored for CMV, and CMV infection associated with human milk will be managed (Fig. 2) [20–23]. If an event occurs where the standard practice requires stopping feeds, such as NEC, the feeding protocol will be stopped for that patient.

**Fig. 2 Fig2:**
[figure not shown]
CMV infection monitoring during human milk feeding

All cases of mortality, NEC, sepsis, and critical incidence reports (including infants receiving the wrong milk, infection that is related to feeds, delays in milk preparation that result in missed feeds, and any other incident clinicians deem concerning) that occur in infants enrolled in the study will be critically reviewed by a Data Safety and Monitoring Committee; the study will stop if safety concerns are raised. Stopping criteria and decisions will be decided by the Data Safety and Monitoring Committee. The Data Safety and Monitoring Committee will consist of the following three people who are experts in the use of human milk to feed infants born preterm and research methodology:
[name], Director of Research, Children’s Hospital of Fudan University, Shanghai, ChinaDr. [name], Director of Neonatology, Children’s Hospital of Fudan University, Shanghai, ChinaDr. [name], Statistician, Children’s Hospital of Fudan University, Shanghai, China

### Outcomes measures

The primary outcome of the study will be a composite of mortality or NEC ≥ stage 2. The secondary outcomes of the study will be mortality before discharge; NEC ≥ stage 2; NEC needing surgery; late-onset sepsis; retinopathy of prematurity (ROP) requiring treatment; bronchopulmonary dysplasia (BPD); change in weight, length, and head circumference; change in weight, length, and head circumference z-scores; time to full enteral feeds (160 mL/kg/day); and number and type of critical incident reports, including feeding errors. NEC will be defined according to Bell’s classification [24]. Sepsis will be defined as isolation of bacterial, fungal or viral organism from blood or cerebrospinal fluid in a symptomatic infant. ROP will be defined according to the International Committee for the Classification of Retinopathy of Prematurity [25]. BPD will be defined as oxygen need at 36 weeks’ postmenstrual age [26]. Weight, weight z-score, length and head circumference will be assessed on a weekly basis until the infant is 9 weeks (63 days) of age.

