### Study population

The study population will include infants born at < 30 weeks’ gestation who never received infant formula, are admitted to one of the 29 participating tertiary NICUs in China, have parents who consent to the study, and have mothers who are willing to provide at least two feeds of fresh milk daily, 7 days a week until the infant is 32 weeks’ corrected age. Infants with major congenital anomalies or receiving palliative care, infants with mothers who are too ill to provide fresh human milk in the first week postpartum or are unable to provide at least two feeds of fresh milk a day, infants with congenital *Cytomegalic virus* (CMV) infection, and infants whose mothers have blood CMV-IgM (+) or CMV-DNA (+) or are unwilling to consent will be excluded. Congenital CMV-infection is defined as positive CMV NAT (or positive viral culture obtained from clinician-ordered testing) in blood or urine within 2 weeks of life [20].

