*Cytomegalic virus* infection acquired from fresh human milk has been discussed as a potential safety concern in preterm infants [48]. However, the issue is controversial, and guidelines vary [49]. Some guidelines recommend that preterm infants are fed pasteurized mother’s own milk because of the potential risk of contamination by CMV. However, this may be unnecessary considering that if a mother is CMV positive, the infant already will have been exposed to CMV *in utero*. We will address this concern in our study by requiring every neonate admitted to the NICU to be tested for CMV and pasteurizing infected milk before use.

Oxidative stress is a major problem for ill infants and for preterm infants in particular; therefore, energy intake and antioxidant defense are crucial for preterm infants’ wellbeing [﻿45﻿]. Very preterm infants have diminished antioxidant capacity and are frequently exposed to oxidative stress from multiple sources such as infection, oxygen therapy, and mechanical ventilation. Furthermore, excess oxygen can secondarily lead to retinopathy of prematurity or chronic lung disease in preterm infants [﻿45﻿]. NEC, intraventricular/periventricular hemorrhage, and retinopathy of prematurity are all thought to be consequences of the imbalance between antioxidant capacity and oxidative stress [50]. Previous studies reported that human milk has important and essential antioxidant components, which may prevent and protect against diseases in infancy [45]. Human milk feeding remains an essential tool to help in the protection against free radicals, oxygen reactive species and oxidative stress, with fresh human milk having been reported to have the highest antioxidant activity [﻿45].

Our study will have some limitations. One limitation is a potential drop-out rate of 10% of enrolled families (based on our pilot study data) [﻿19﻿] due to factors such as time constraints. To minimize the potential bias from families leaving the study, we will use intention-to-treat analysis. If applicable, we will also conduct regression adjusted for propensity score estimated based on the infant and NICU characteristics available. Last, in China, approximately 17% of infants born preterm per year are discharged against medical advice and die at home. These infants will be included in our intention-to-treat analysis. To address this concern, we will perform a subgroup analysis of the primary outcome that only includes infants who were actively treated.

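### Counting viral isolates as sepsis puts milk-acquired CMV, a named hazard of fresh milk, into the same yes/no secondary outcome as the bacterial and fungal infections fresh milk is meant to prevent

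*Protocol article*

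**What the plan says.** Outcomes measures lists among the secondary outcomes "NEC needing surgery; late-onset sepsis; retinopathy of prematurity (ROP) requiring treatment". The same section gives one definition for the sepsis part: "Sepsis will be defined as isolation of bacterial, fungal or viral organism from blood or cerebrospinal fluid in a symptomatic infant". Viral organisms thus count on the same footing as bacteria and fungi, subject to two limits: the specimen is blood or CSF, and the infant is symptomatic.

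On CMV, the Safety section states "Every neonate admitted to the NICU will complete the TORCH screen for toxoplasma, rubella, cytomegalovirus, and herpes simplex", and then "During the fresh milk feeding, human milk will be monitored for CMV, and CMV infection associated with human milk will be managed". The caption of Fig. 2, to which that sentence refers, reads "CMV infection monitoring during human milk feeding"; the figure itself is not shown. The Discussion accepts that CMV from fresh milk has been raised as a safety concern, calls the issue controversial, and says it will be handled by "requiring every neonate admitted to the NICU to be tested for CMV and pasteurizing infected milk before use". Study population excludes infants with congenital CMV infection, and "infants whose mothers have blood CMV-IgM (+) or CMV-DNA (+) or are unwilling to consent will be excluded".

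The Feeding intervention section defines fresh milk as milk that has been neither frozen, chilled nor pasteurized. The Background expects it to protect against infection as well as NEC, and the Discussion lists sepsis among the outcomes to be evaluated.

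**The concern.** The intervention has a hoped-for effect on infection (fewer bacterial and fungal infections) and a feared one (transmission of CMV). The sepsis definition adds the two with the same sign. A null result could then mean no effect, or a benefit and a harm of similar size; a modest apparent benefit could be a larger benefit partly cancelled. The between-arm table could not tell these apart. This follows from the definition and would remain if every infant in both arms were tested identically.

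A second question is ascertainment. The Safety text attaches CMV monitoring to fresh-milk feeding, while the caption refers to human-milk feeding, which both arms receive. If monitoring did differ by arm, the viral part of the outcome would be looked for more closely in one arm than in the other.

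**Working it through.** **1. What the definition admits.** An infant who acquires CMV from milk, has symptoms and has virus isolated from blood or CSF meets every element of the definition. A CMV-positive milk sample, a positive urine test, or a positive blood test in an infant without symptoms does not. So the viral limb is narrower than all CMV detections, but it includes the cases that matter clinically.

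**2. How far offsetting could go (illustration).** The protocol states no sepsis rate or CMV rate, so there is no figure of its own to reproduce. Inputs from the document: n = 1549 per arm (Sample size), chi-square test, two-sided 0.05 (Statistical analysis). Assumed: a bacterial or fungal rate of 10% or 20% in controls; a true risk ratio of 0.75 on that part; a net excess c of symptomatic, blood- or CSF-positive CMV in the fresh-milk arm, in infants not otherwise counted.

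Formula: z = (p1 − p2) / √[2p̄(1 − p̄)/n], with p̄ the mean of p1 and p2; power ≈ Φ(z − 1.96).

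Worked case, 10% base, c = 0: p2 = 0.075, p̄ = 0.0875, standard error = √(2 × 0.0875 × 0.9125 / 1549) = 0.01015, z = 0.025 / 0.01015 = 2.46, power = 69%.

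| Control rate | c (points) | Fresh-arm rate | Apparent risk ratio | Power |
|---|---|---|---|---|
| 10% | 0 | 7.5% | 0.75 | 69% |
| 10% | 1 | 8.5% | 0.85 | 30% |
| 10% | 2 | 9.5% | 0.95 | 7% |
| 20% | 0 | 15% | 0.75 | 96% |
| 20% | 1 | 16% | 0.80 | 83% |
| 20% | 2 | 17% | 0.85 | 58% |

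One point is 0.01 × 1549, about 15 infants. At the 10% base, full cancellation needs c = 2.5 points, equal to the whole benefit.

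**3. Is testing unequal by arm?** Set side by side:
- The Safety text on monitoring refers to fresh-milk feeding, and the specimen it names is milk, not infant blood.
- The Fig. 2 caption refers to human-milk feeding and names no arm.
- The TORCH screen and the Discussion's CMV test cover every neonate, but as tests of admitted infants; neither says that later monitoring is the same in both arms.
- Care teams and the outcome collector are blinded to milk type (Randomization and blinding).

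A positive milk result could prompt an infant blood test, but no text says so. The two statements on monitoring differ; one-sided infant testing does not follow from them.

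**4. If detection were one-sided (conditional).** Suppose bacterial or fungal sepsis is equal in the two arms and 1, 2 or 3 points (about 15, 31 or 46 infants) are added in the fresh-milk arm by detection alone. At an assumed 15% base, z = 0.77, 1.52 and 2.25, and the chance of a significant false excess is 12%, 33% and 61%. At 10% it is 15%, 43% and 75%; at 20%, 10%, 28% and 53%. These figures have no application if testing is equal.

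**The case against.** The strongest reply is that the mixture is likely to be small. CMV-IgM or CMV-DNA positive mothers and congenitally infected infants are excluded, and infected milk is to be pasteurized before use. Symptoms and a blood or CSF isolate are both required. Milk-acquired CMV is moreover a real consequence of the intervention, so counting it is not bias in itself. All of this stands, and it limits the size. It does not remove the point: the protocol still plans to monitor for and manage milk-associated CMV, so it does not treat the risk as nil, and a real harm is better reported as such than netted against a benefit.

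Three stronger readings are tempting and are not supported.

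- *That infants in the fresh-milk arm have extra CMV testing.* The monitored specimen is milk, the caption and the Discussion name no arm, the figure that may settle the schedule is not shown, and care teams are blinded. It is a possibility to close off, not a finding.
- *That infections at any age, including those before the first feed, are counted.* The outcome is already named late-onset; the numeric cut-off is detail that an article may leave to the full protocol. Because enrollment precedes the first oral feed, such infections could not be caused by the milk and should balance by randomization. At most they dilute: 1 to 3 points added to both arms would move a risk ratio of 0.75 to 0.77–0.81 at an assumed 10% base, and power from 69% to 65–58%.
- *That the mixture distorts the stopping decision.* The Safety section has the committee review cases critically and lists feed-related infection as its own type of incident, so the committee has another view of these events.

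**Conclusion.** The point holds as a fault in the construction of one secondary outcome: by an explicit rule, late-onset sepsis combines infections the intervention should reduce with one it might transmit. The cost is loss of interpretability and possibly of power. Under the assumptions shown, a net CMV excess of 1 point would take power from 69% to 30% at a 10% base, or from 96% to 83% at a 20% base; with the exclusions and pasteurization in place the true excess may well be smaller. Neither the base rates, nor the 0.75 ratio, nor the CMV excess comes from the documents.

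The disagreement between the Safety text and the Fig. 2 caption is real on its face and should be resolved. Whether it reflects unequal ascertainment cannot be determined from what is shown, so the false-excess figures are illustrations only. The primary composite of mortality or NEC is not affected. The change is worth making because it is cheap, not because a main conclusion depends on it.

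**What to change.** 1. For the between-arm comparison, define late-onset sepsis as a bacterial or fungal isolate from blood or CSF in a symptomatic infant, and remove viral organisms.
2. Report postnatal CMV infection separately by arm as a safety outcome.
3. Reconcile the Safety text with the Fig. 2 caption, and state that CMV ascertainment (triggers, specimens and timing, as the sponsor sets them) is the same in both arms.

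Cost: one reworded definition, one extra table row and slightly fewer sepsis events. If monitoring is at present confined to one arm, the third item may add some CMV tests. The first item needs no extra testing and by itself removes the mixture, and any effect of unequal CMV detection, from the sepsis comparison.

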## Background

Necrotizing enterocolitis (NEC) is a severe inflammatory disorder of the intestine that primarily affects very low birth weight (< 1500 g) or very preterm infants (≤ 32 weeks’ gestation); it is also the leading cause of death in the neonatal intensive care unit (NICU) [1, 2]. Between May 1, 2015, and April 28, 2018, we found that the incidence of mortality in infants born at < 30 weeks’ gestation at 25 hospitals in China was 25%, and the incidence of NEC was 6.2% [[name], written communication, October 2018]. Elsewhere, the overall mortality from NEC was reported to range from 15 to 30%, with more severe cases of NEC resulting in a higher mortality rate. For infants who survive, a significant risk exists for long-term complications and morbidity, including impaired neurodevelopment [1, 2].

Currently, no known effective treatment exists for NEC. Infants are initially managed medically through bowel rest (cessation of oral feeds), abdominal decompression, administration of broad-spectrum antibiotics, and provision of supportive care including parenteral nutrition, ventilator support, and blood transfusions as necessary. Should bowel perforation occur, then surgery is required to remove damaged tissue and gas build up through laparotomy, primary peritoneal drainage, or both [1, 2].

The World Health Organization and others have advocated for the use of mother’s own milk to prevent NEC [3–5]. Human milk contains both nutritional components (e.g., proteins, amino acids, fats, carbohydrates, vitamins, and minerals) and bioactive components (e.g., live immune cells, cytokines, hormones, and growth factors) that have antimicrobial and anti-inflammatory properties [6, 7]. More recently, Hassiotou (now Kakulas) et al. [8] showed that human milk is a rich source of pluripotent stem cells that, when ingested by the infant, enter the blood stream and are incorporated into the major organ systems of the infant. Although their exact function still remains unknown, breast milk stem cells possibly benefit the infant through actively participating in growth and/or regeneration. The current evidence strongly suggests that fresh human milk may have a significant protective effect against both infection and NEC [9].

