### Statistical analysis

Data from the study will be analyzed on an intention-to-treat basis. Patient characteristics at baseline will be summarized within each of the groups using the descriptive statistical methods suggested by the CONSORT statement for randomized clinical trials. To examine the difference in the rate of the primary outcome between the control and fresh human milk groups, we will use the chi-square test. We will compare the secondary outcomes of the control and fresh milk groups using the chi-square test or Fisher exact test, as appropriate, for categorical variables and the Student T test or Wilcoxon Rank Sum test, as appropriate, for continuous variables.

As secondary analyses, we will also, if applicable, determine whether a variation exists in the treatment effect across the centers/NICUs by presenting the effects by individual centers/NICUs graphically. If variation is observed, we will further compare the binary outcomes using the Cochran-Mantel-Haenszel test to account for the effect of center, as well as conducting fixed-effect logistic regression (for binary outcomes) or linear regression (for continuous outcomes) without including treatment-center interaction term. The fixed-effect model including treatment-center interaction term will be further applied to examine the heterogeneity of the effect across centers when the variation in the center-effect is identified. If variation exist in the center-effect but no heterogeneity of the effect is observed, a marginal logistic or linear regression model with generalized estimating equations (GEE) approach will be applied to estimate the main treatment effect to account for the center effect. If the heterogeneity of the effect is observed, subgroup analysis stratified by the homogeneous centers using marginal models with GEE approach will be applied if applicable.

To examine whether a variation exists in the treatment effect across gestational age group (i.e., GA < 28 vs GA: 28–30), birth weight group (i.e., BW < 1000 g vs BW: 1000-1500 g) or upon receipt of probiotics, fixed-effect logistic or linear models will be used that include GA (or BW or probiotic) group and the interaction between treatment and GA group (or BW or probiotic), if applicable.

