In China, approximately 17% of infants born preterm die at home following discharge against medical advice [[name], written communication, October 2018]. Since we are using intention-to-treat analysis in our study, these infants will be included in our analysis. However, we will perform a subgroup analysis that only includes infants who were actively treated, which includes 1991 infants per year on average [[name], written communication, October 2018]. The primary outcome rate is 17%, on average, for infants who are actively treated; therefore, we estimate that a total sample size of 2292 infants (1146 per arm) will achieve an 80% power to detect at least a 25% relative reduction in the incidence of the primary outcome in the fresh milk group when compared to the control group.

We will also apply linear or nonlinear mixed-effect models for the longitudinal secondary outcomes (weight or change in weight z-score over time) to compare the rate of the change in the outcomes between the two groups, adjusted for the infant- and NICU- level characteristics if applicable. For secondary outcomes, no adjustment for multiple comparisons will be conducted.

For the primary outcome, to minimize possible bias due to drop out or missing data, we will also, if applicable, conduct logistic regression adjusted for propensity score estimated based on the infant and NICU characteristics available. A two-sided *p* value of < 0.05 will be used to determine the statistically significant difference.

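### BPD and ROP are tested as stand-alone yes/no outcomes with no rule for infants who die first, so a survival benefit could mask or reverse a lung or eye benefit

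*Protocol article*

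**What the plan says.** In the protocol article, *Outcomes measures* lists BPD and ROP requiring treatment as separate secondary outcomes, next to mortality before discharge. For BPD the only rule is "BPD will be defined as oxygen need at 36 weeks’ postmenstrual age".

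*Statistical analysis* opens with "Data from the study will be analyzed on an intention-to-treat basis" and compares the secondary outcomes of the two "groups using the chi-square test or Fisher exact test, as appropriate, for categorical variables". On infants taken home against medical advice who die there, the same section says "Since we are using intention-to-treat analysis in our study, these infants will be included in our analysis".

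The analysis restricted to actively treated infants is described in the *Discussion* as one for the primary outcome: "we will perform a subgroup analysis of the primary outcome that only includes infants who were actively treated".

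On mortality, *Background* reports that "the incidence of mortality in infants born at < 30 weeks’ gestation at 25 hospitals in China was 25" per cent.

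The article gives no denominator for BPD or ROP, no rule for death before assessment, and no composite of death with either outcome.

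**The concern.** The primary outcome joins death with NEC, so an infant who dies before NEC can appear is still an event. BPD and ROP, which are seen later still, do not have this protection.

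An infant who dies at 29 weeks on a ventilator has no oxygen need at 36 weeks. There are two ways to handle that infant in a stand-alone test:

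- **Keep in the denominator as no BPD.** The death then counts the same as a healthy survivor in room air.
- **Drop.** The comparison is then confined to survivors, a group formed after randomisation by an event that the treatment is expected to change.

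Either way, if fresh milk saves lives, the arm that does better on survival can look worse on BPD, or a real lung benefit can be hidden. If fresh milk raised mortality, the distortion would run the other way and flatter it.

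**Working it through.** **Inputs from the article.** n = 1549 per arm, 16% relative reduction, two-sided 0.05 (*Sample size*, *Statistical analysis*); mortality 25% (*Background*).

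**Assumptions.** The documents give no BPD rate. BPD risk among infants who survive in either arm is taken as b = 30%, range 20-40%. The 16% reduction, planned for death or NEC, is applied wholly to mortality: m0 = 0.25, m1 = 0.25 × 0.84 = 0.21. All these deaths are taken to precede 36 weeks. Fresh milk has no effect on BPD itself. bs is the BPD risk of the extra survivors, set to b or 2b; no passage supports the doubling, which only illustrates sicker extra survivors.

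**The plan's own figure.** 29% v 29% × 0.84 = 24.36% at 80% power needs 1426 per arm, or 1468 with continuity correction. 1468 / 0.95 = 1546, against 1549 stated. The sample size reproduces closely, so 1549 is used below.

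**Formulas.**
- All randomised, deaths counted as no BPD: control (1 − m0)b; fresh milk (1 − m0)b + (m0 − m1)bs.
- Survivors only: the same quantities divided by (1 − m0) and (1 − m1).
- Death or BPD: m0 or m1 plus the all-randomised BPD rate.
- Chance of significant false harm: P(Z > 1.96 − difference/SE), unpooled SE. It is 2.5% when there is no bias.

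**Example, b = bs = 30%.** Control 0.75 × 0.30 = 22.5%. Fresh milk 22.5% + 0.04 × 0.30 = 23.7%. SE = √[(0.225 × 0.775 + 0.237 × 0.763)/1549] = 0.0151. Difference/SE = 0.012/0.0151 = 0.79. P(Z > 1.17) = 12%.

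**Results at b = 30%, control v fresh milk (range for b = 20-40%).**

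| Handling of deaths | Extra survivors | Rates | False harm |
|---|---|---|---|
| In denominator, no BPD | same risk | 22.5% v 23.7% | 12% (9-16%) |
| In denominator, no BPD | double risk | 22.5% v 24.9% | 35% (23-48%) |
| Dropped | same risk | 30.0% v 30.0% | 2.5% |
| Dropped | double risk | 30.0% v 31.5% | 12% (9-17%) |
| Death or BPD | same risk | 47.5% v 44.7% | right direction |
| Death or BPD | double risk | 47.5% v 45.9% | right direction |

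**How many infants.** At 25% mortality, 0.25 × 1549 ≈ 387 infants in an arm would die.

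**What cancels it.** With deaths kept and equal risk, apparent BPD rises by the ratio 0.79/0.75 = 1.053. A true relative fall of 1 − 0.75/0.79 = 5.1% in survivor BPD risk brings it back to level.

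**Fewer preventable deaths.** *Statistical analysis* says "approximately 17% of infants born preterm die at home following discharge against medical advice". If those 17 points lie within the 25% and milk cannot prevent them (an assumption), 8 points remain and m1 = 0.17 + 0.08 × 0.84 = 23.7%. With deaths kept and b = 30%, the artefact is +0.4 points (false harm 4%) at equal risk and +0.8 points (7%) at double risk.

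**Lower mortality.** With control mortality of 15-20%, the 16% reduction and deaths kept, false harm is 5-12% at equal risk and 10-33% at double risk, over b = 20-40%.

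**The case against.** **The article never says that deaths are scored as free of BPD.** This stands. A reader might infer it from the intention-to-treat wording and from the statement that infants who die at home stay in the analysis. But intention-to-treat fixes the arm in which an infant is analysed, not the coding of an outcome that cannot be observed. *Data collection* itself treats BPD as assessable only beyond 32 weeks, so treating these infants as not assessable is as natural a reading. That reading brings the survivors-only problem instead.

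**A survivors-only test has no bias when the extra survivors carry the same BPD risk.** Correct, as the table shows. It is biased when they are sicker, and the trial cannot observe which infants are the extra survivors.

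**The mortality inputs are generous.** Partly correct. The 25% is historical and not timed against 36 weeks. The trial excludes infants with major anomalies or in palliative care. The 16% belongs to the composite. On the other side, if the planned 29% composite rate and the 6.2% NEC rate describe the same infants, mortality is at least 29 − 6.2 = 22.8%. If that composite rate is the one at 32 weeks, those deaths precede 36 weeks.

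**A denominator for a secondary outcome can be left to the analysis plan.** A missing denominator alone would not be a finding. Here, though, the article fixes the outcome definition, the analysis basis and the test, and neither way of counting deaths makes that stand-alone comparison safe.

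**Mortality is reported separately, so readers would see a survival gain beside the BPD result.** True, and it limits the harm. It does not make the BPD test itself interpretable.

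**Conclusion.** The point holds in a limited form. BPD and ROP requiring treatment are compared as stand-alone outcomes although death prevents both, and the text does not say how infants who die first are counted. With deaths kept as non-events, the central illustration is +1.2 points of apparent BPD and about a 12% chance of significant false harm. It rests on an assumed survivor BPD risk and on the full 16% reduction falling on mortality before 36 weeks. The artefact shrinks if fewer deaths are preventable or occur before 36 weeks.

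Two stronger readings are not supported. One is that the plan counts about a quarter of infants as free of BPD; it does not state this, and the 25% is not established for enrolled infants. The other is that a true survival benefit would necessarily appear as more BPD. It would only tend to: a true relative fall of about 5% in survivor BPD risk offsets the equal-risk artefact, and the *Discussion* expects human milk to lower BPD. The 35% figure needs both deaths counted as no BPD and a doubled risk in the extra survivors.

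No size is given for ROP, because the documents contain no rate; the mechanism is the same. Only secondary outcomes are affected. The primary analysis and sample size stand.

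**What to change.** In *Outcomes measures* and *Statistical analysis*:

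1. Add *death before 36 weeks' postmenstrual age or BPD* and *death or ROP requiring treatment*, analysed in all randomised infants, as the between-arm comparisons on which any treatment claim rests.
2. Keep BPD and ROP, reported alongside among infants alive at assessment, with that denominator stated and the result interpreted cautiously.
3. State that infants who die before assessment are not scored as free of BPD or ROP.

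The cost is wording only: deaths are already collected, and no visit or extra infant is needed. The downside is that each composite is partly driven by death and dilutes a lung- or eye-specific effect; the components shown alongside cover that. The change should be made before any analysis by treatment arm, so that the denominator is not chosen after the results are seen.
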